#### Allocation

Upon reception of the signed Information and Consent forms by email, consecutive referrals will be randomly allocated by computer algorithm to one of the two modalities at point of entry into the study on acceptation into the protocol using a computerized program (eg, randomization.com). At this entry point, the participant will have been evaluated, diagnosed, met inclusion criteria, and given formal consent for the randomization procedure. To ensure a balance in the allocation for the strata and thus control the risk of a secular trend in the composition of groups, random block sizes in a random order will be used (3, 6, 9, etc). Participants will thus be randomly allocated to the trial arm (n=20, 2 groups of 10) or control arm (n=10), and will be identified by a randomly assigned identification number. Among those allocated to the experimental groups, 10 patients with psychotic disorders will be randomly selected to be part of the transitional support group for patients with psychotic disorders, and 10 patients with anxiety or mood disorders will be randomly selected to be part of the transitional self-help group for patients with anxiety or mood disorders. It will be the same for the control group; 5 patients with psychotic disorders will be randomly selected to be part of the control group for patients with psychotic disorders, and 5 patients with anxiety or mood disorders will be randomly selected to be part of the control group for patients with anxiety or mood disorders. In both cases, those who have not been selected will be placed on a substitute list in the event of withdrawal of a selected patient, who will be replaced at random by one of the corresponding substitutes.

The groups will be studied together and separately: the experimental group for patients with psychotic disorders (n=10) will be compared to the control group for patients with psychotic disorders (n=5); the experimental group for patients with anxiety or mood disorders (n=10) will be compared to the control group for patients with anxiety or mood disorders (n=5); and the combined experimental group for patients with psychotic disorders and for patients with anxiety or mood disorders (n=20; 2×10) will be compared to the combined control group for patients with psychotic disorders and anxiety or mood disorders (n=10).

This study will be reported following the CONSORT (Consolidated Standards of Reporting Trials) guidelines [91] and registered before the enrollment of the first participant (eg, ClinicalTrials.gov).

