#### Planned Trial Interventions

##### Control Intervention

When a person shows up at the Emergency Department of IUSMM for the first time, he or she is systematically approached by a research nurse after a first medical authorization is granted for that person to be approached (sometimes this authorization is not granted for medical or security reasons). The research nurse then explains the objectives of the Signature Bank project and invites the person to participate. Those who agree to participate sign the Information and Consent Form (T1), fill out a series of questionnaires, including ones on sociodemographics; consent to the taking of biological samples; and asked if they are willing to be contacted for other research purposes (like our own study). Then, as with any other IUSMM patients, they are evaluated by the Evaluation and Liaison Module during their hospital stay. A diagnostic is established or confirmed by ward psychiatrists and coded according to the WHO International Classification of Disease–10th Revision (ICD-10) [79]. Based on the diagnosis (or diagnoses), after discharge (T2), they are referred to a specialized outpatient clinic (T3). Whether for psychotic disorders or for anxiety and mood disorders, pharmacotherapy, psychotherapy, or a combination of both are then offered in accordance with the guidelines of the Royal College of Physicians and Surgeons of Canada. Of the Signature Bank participants diagnosed with psychotic disorders, or anxiety or mood disorders, and who consent to participate in our study, half will receive only the control intervention, while the other half will also receive our experimental PSW-led online group intervention (random allocation control/experimental intervention ratio=2:1).

Inclusion criteria include patients recruited from the Signature Bank data collection project diagnosed with (1) schizophrenia and psychotic disorders (ICD F20-F29), or with (2) anxiety or mood disorders (ICD F30-F49), (3) aged 18 years old or more, and (4) who have already consented to be contacted by telephone to be invited by our team to participate in this pilot study. Exclusion criteria include (1) active suicidal intentions, (2) marked cognitive impairment, and (3) no access to an electronic device with a webcam and microphone to participate in the online transitional peer support group.

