#### Quantitative Analyzes

Baseline characteristics will be summarized, including for the measures of clinical recovery (see the *Outcome Measures at Follow-up* section), the Recovery Assessment Scale, the Citizenship Measure (personal-civic recovery), the COVID-19 Stress Scales, and the Bem Sex Role Inventory. All participants with data at baseline (T1) and follow-up will be included in the analyses. We will compare within-patient change from baseline to intervention versus control group in the study outcome measures using the Student paired sample *t* test. The analysis will run on intervention and control practices separately so as to explore practice level impact on the differences in outcomes. Comparison of confidence interval and effect size between groups will be assessed.

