**Total eligible participants (N=92)**		
	Participants with AMD^a^	31 (33.7)
	Participants with PD^b^	61 (66.3)
**Total eligible participants who agreed to receive the ICF^c^ by email (N=92)**		54 (58.7)
	Participants with AMD (n=31)	23 (74.2)
	Participants with PD (n=61)	31 (50.8)
**Total eligible participants who returned the signed ICF (n=54)**		36 (66.7)
	Participants with AMD (n=23)	17 (73.9)
	Participants with PD (n=31)	19 (61.3)
**Total eligible participants who completed the questionnaires at T1 (n=36)**		32 (88.8)
	Participants with AMD (n=17)	16 (94.1)
	Participants with PD (n=19)	19 (100.0)
**Total eligible participants who completed the questionnaires at T2 (n=30)**		24 (80.0)
	Participants with AMD in the experimental group (n=10)	7 (70.0)
	Participants with PD in the experimental group (n=10)	10 (100.0)
	Participants with AMD or PD in the control group (n=10)	7 (70.0)

^a^AMD: anxiety and mood disorders

^b^PD: psychotic disorders.

^c^ICF: Information and Consent Form.

**Table 2 table2:** Calendar of activities.

Date	Activity	
	Convergent and Concurrent Validity Between Clinical Recovery and Personal-Civic Recovery	Effects of Online and Recovery-Oriented Peer Support Groups Facilitated by Peer Support Workers
	ClinicalTrials.gov ID NCT04125030	ClinicalTrials.gov ID NCT04445324
September 2019 to March 2020	Study suspended due to the COVID-19 pandemic 92 eligible participants completed the study	—^a^
April-May 2020	—	Writing and submission of the research protocol to the institutional review board
June 2020	—	Institutional review board approval of research protocol
July 2020	Submission of the study protocol for publication in a peer-reviewed journal	Submission of the study protocol for publication in a peer-reviewed journal
August 2020	—	Recruitment of study participants among those 92 from the previous validation study Precompletion of measures (T1)
September to October 2020	Publication of the research protocol [100]	10 weekly peer support groups for patients with psychotic disorders 10 weekly peer support groups for patients with anxiety or mood disorders
November 2020	Data analyses	Postcompletion of measures (T2) Addenda to study protocol Submission of the revised study protocol for publication
December 2020	Submission of the study’s main conclusions for publication in an open access peer-reviewed journal	Data analyses Submission of the study’s main conclusions for publication in an open access peer-reviewed journal

^a^Not applicable.

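### Allocation is tied to receipt of the consent form and does not require the T1 questionnaires first, so self-rated baselines may be given, and patients may be lost, after allocation

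*Protocol article*

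**What the plan says.** The Allocation section sets the moment of randomisation: "Upon reception of the signed Information and Consent forms by email, consecutive referrals will be randomly allocated by computer algorithm". It then describes the state of the participant at that moment: "At this entry point, the participant will have been evaluated, diagnosed, met inclusion criteria, and given formal consent for the randomization procedure". The study questionnaires are not in that list. The word evaluated most plausibly refers to the clinical work-up described under Control Intervention, where patients entering the Signature Bank are followed in hospital: "they are evaluated by the Evaluation and Liaison Module during their hospital stay".

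Table 1 takes the 36 returned consent forms as the denominator for baseline completion: "Total eligible participants who completed the questionnaires at T1 (n=36". Table 2 places "Precompletion of measures (T1" in the same month as recruitment (August 2020), with the groups starting in September.

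The Quantitative Analyzes section defines who is analysed: "All participants with data at baseline (T1) and follow-up will be included in the analyses". The planned comparison uses within-patient change from baseline.

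The section on protecting against bias limits what clinical staff and peer support workers are told about scores. It says nothing about when participants learn their arm.

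**The concern.** The Recovery Assessment Scale and the Citizenship Measure, which carry the primary outcome, are filled in by the patient. The contrast is an online support group against usual care, which cannot be masked once the groups begin. If a patient already knows the arm when rating T1, expectation or disappointment can move the baseline, and the change score inherits that movement.

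The second risk is selection. A patient who is allocated and then does not complete T1 has no baseline and leaves the analysis set. If such losses differ between arms, the groups compared are no longer the groups randomised.

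The study is meant to prepare a definitive randomised trial. A bias caused by the order of steps would not shrink with a larger sample if the same order were carried forward.

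**Working it through.** No sample-size or power figure is involved. The check covers the order of steps and the counts in Table 1.

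**Order of steps, sections side by side**
- Allocation: the trigger is receipt of the signed form, and T1 is not listed as complete.
- Table 1: T1 is counted among those who returned the form, so T1 follows consent.
- Taken together, the text as written gives consent, allocation, T1. This order is inferred; no sentence states outright that T1 comes after allocation.

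**Counts in Table 1**
- Consent forms returned ("Total eligible participants who returned the signed ICF (n=54"): 36/54 = 66.7%, as printed.
- T1 total row: 32/36 = 88.9%, printed as 88.8 (a truncation).
- T1 subgroup rows: 16/17 = 94.1% and 19/19 = 100.0%, both as printed. Their sum is 16 + 19 = 35, not 32, so the total row cannot be reproduced from its parts.
- T2 ("Total eligible participants who completed the questionnaires at T2 (n=30"): 7 + 10 + 7 = 24 and 24/30 = 80.0%, as printed.

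**Loss between consent and T1**
- From the total row: 36 − 32 = 4, and 4/36 = 11.1%.
- From the subgroup rows: 36 − 35 = 1, and 1/36 = 2.8%.
- T1 is not shown by arm. If all 36 had been allocated 2:1 (24 and 12, an assumption), four losses falling in a single arm would be 4/24 = 16.7% of the experimental arm or 4/12 = 33.3% of the control arm. These are outer limits, not estimates.

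**Size of a baseline shift (illustration only; the shift is assumed)**
- Let knowledge of the arm move T1 by *d* in one arm, with a fraction *f* of that shift still present at T2. The difference in change then moves by *d*(1 − *f*) in absolute size.
- With *d* = 0.2 SD and the SD of 0.78 given for the Recovery Assessment Scale under Recruitment, *d* = 0.2 × 0.78 = 0.156 points.
- The resulting movement is 0.156 points if *f* = 0, 0.078 if *f* = 0.5, and 0 if *f* = 1.
- For comparison, the standard error of a baseline mean difference with 20 and 10 patients is 0.78 × √(1/20 + 1/10) = 0.30 points. A shift of this size could not be detected in the pilot's own data.

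**The case against.** A reader might infer that patients did rate their baseline knowing their arm. The documents do not support that. Bias in a self-rating needs disclosure, not merely a computer assignment, and nothing states when the arm was disclosed. A condensed article may well leave that detail to the full protocol.

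The documents also leave room for the opposite order. The Allocation section adds a second random selection after allocation, with a substitute list, so a patient's final place need not be known when the form arrives. Table 1 shows consent and T1 by diagnosis only; arms first appear at T2, where the denominators total 30. The sequence 36 consented, 32 with T1, 30 placed is compatible with groups formed from T1 completers. For the same reason a reader should not infer that one or four patients were lost after randomisation: that holds only if all 36 were allocated before T1, and the two rows disagree. The size of any baseline shift is assumed, and it cancels in part if it persists to T2.

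All of this stands, and it limits the point to what may have happened. It does not remove the point, because the article fixes a rule, allocation at consent, that permits both problems. If practice differed, the text misdescribes the procedure and still needs correcting.

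**Conclusion.** The concern holds as a weakness in the stated order of steps, not as a demonstrated bias. As written, allocation occurs on receipt of consent without T1 as a precondition, while T1 follows consent. Self-rated baselines may therefore be given with knowledge of the arm, and pre-baseline losses may be post-allocation losses that the analysis rule removes.

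The documented size is a loss of 4 of 36 or 1 of 36 between consent and T1, depending on which Table 1 row is right, with the split by arm unknown. The size of any shift in the baseline ratings cannot be derived from the documents.

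The conclusion rests on two readings: that evaluated means the clinical evaluation and not the study questionnaires, and that the Allocation section describes the procedure actually used. The point is worth acting on because the correction is nearly free.

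**What to change.** In the Allocation section, state the order as signed consent, then T1 questionnaires complete, then randomisation 2:1 within each diagnosis. If allocation has to stay at consent, state at least that the arm is not disclosed until T1 is complete. The calendar allowed for this: T1 was in August and the groups began in September.

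Recruitment is finished, so the order can no longer be changed for these patients. Use the addenda foreseen in Table 2 and the main report to:
- state the order actually followed and when participants learned their arm;
- report T1 completion by arm, including anyone allocated who never completed T1;
- reconcile the T1 total of 32 with the subgroup sum of 35.

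Write the corrected order into the protocol of the future randomised trial.

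The cost is a sentence of protocol text and one extra row in the participant-flow table, with no added visit. The downside is that patients learn their arm slightly later.

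### Capping controls at five per diagnosis sets aside about two patients randomised to control, at a small cost in precision (between-arm SE about 6% larger than necessary, at most)

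*Protocol article*

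**What the plan says.** All places are in the protocol article. The Allocation section randomises each consenting patient at entry and fixes the arm sizes: "Participants will thus be randomly allocated to the trial arm (n=20, 2 groups of 10) or control arm (n=10"). It then selects within each arm. For the experimental arm it takes 10 patients per diagnosis. For the control arm, "5 patients with psychotic disorders will be randomly selected to be part of the control group for patients with psychotic disorders". The same number is taken for the other diagnosis. For both arms, "those who have not been selected will be placed on a substitute list in the event of withdrawal of a selected patient", and a substitute of the same kind, drawn at random, replaces anyone who withdraws. The planned comparisons are 10 with 5 in each diagnosis and 20 with 10 overall.

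The Control Intervention section describes the control condition as the usual outpatient treatment. The Recruitment section contacts patients until 30 consent forms are back. Table 1 reports 36 signed forms (17 anxiety or mood, 19 psychotic), but its T2 row has a denominator of 30 (10, 10 and 10). The Quantitative Analyzes section includes everyone with baseline and follow-up data.

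**The concern.** The workshops run in groups of 10, which explains a ceiling on the experimental side. No such constraint applies to controls, and the article gives no reason for stopping at 5 per diagnosis. A control-arm substitute is someone who has consented, has been randomised to control, and could simply be followed as a control from the start.

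The control arm is the smaller side of the comparison and contributes most to its standard error: 1/10 of the variance term, against 1/20 from the experimental arm. The Discussion relies on the between-arm contrast to separate the intervention from the pandemic, and the Principal Research Questions section wants data for a later randomised trial. Leaving out randomised controls who need no further recruitment gives up precision for no stated benefit.

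**Working it through.** **Inputs.** Group places 20 and controls 10 (Allocation). Ratio 2:1 experimental to control (Abstract and Allocation). Signed consents 36 = 17 + 19 (Table 1). T1 completers 32 in the total row, although the subgroup rows give 16 + 19 = 35 (Table 1). Recruitment stop at 30 forms (Recruitment).

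**The plan's own figure.** 30 × 1/3 = 10 controls, and 5 + 5 = 10. Both agree. The article states no alpha, power or effect size, so there is no power calculation to reproduce.

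**Patients set aside.** 36 − 30 = 6 consenting patients lie outside the planned 30. At 2:1, 36 patients split 24 : 12. So about 24 − 20 = 4 of the six would be experimental-arm substitutes and about 12 − 10 = 2 would be control-arm substitutes. By diagnosis, 19/3 = 6.3 and 17/3 = 5.7 patients would be control-allocated, against the 5 and 5 kept.

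**Precision.** With equal SD in the two arms, SE/SD = √(1/n_exp + 1/n_ctrl). The experimental side stays at 20 because its seats are limited.

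| Controls | Basis | SE/SD | Change |
|---|---|---|---|
| 10 | the plan, or recruitment stopped at 30 | √(1/20 + 1/10) = 0.387 | 0 |
| 10.7 | 32/3, T1 total row | √(1/20 + 1/10.67) = 0.379 | −2% |
| 11.7 | 35/3, T1 subgroup rows | √(1/20 + 1/11.67) = 0.368 | −5% |
| 12 | 36/3, all consents | √(1/20 + 1/12) = 0.365 | −6% |

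Within one diagnosis, going from 10 v 5 to 10 v 6 takes SE/SD from 0.548 to 0.516, also −6%.

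**After dropout.** Table 1 shows 17 experimental and 7 control patients at T2. At the same 70% control completion, 12 controls would give 8.4. SE/SD goes from √(1/17 + 1/7) = 0.449 to √(1/17 + 1/8.4) = 0.422, again −6%.

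**Detectable difference.** Assuming two-sided alpha 0.05, 80% power and a t test, it falls from 1.12 SD (20 v 10) to 1.06 SD (20 v 12).

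**The case against.** The strongest reply is that the plan contains no surplus at all. Recruitment was to stop at 30 forms, which at 2:1 gives 10 controls. The 36 is a recruitment result, seen afterwards. That stands as a limit on the size of the point. It does not remove it, because the Allocation section itself provides for unselected patients in both arms, and Table 1 shows that more than 30 consented.

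A second reply is that some of the six may already be in the T2 denominator as replacements. Table 1 does not say. So one cannot claim that all six contributed nothing, only that a control-arm substitute does so if never called.

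A third is that this is a feasibility study with no power target, and that even the improved comparison detects only very large effects. That also stands, and it is why the point is minor.

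A reader might infer something stronger: that 36 − 20 = 16 controls were available and the cap cost 13% in standard error (0.387 to 0.335). The documents do not support this. Under the stated allocation about 4 of the 6 surplus patients would have been randomised to the experimental arm, and counting them as controls afterwards would break the randomisation. Sixteen controls would need a different design, with a single draw per diagnosis at about 1.25:1 and no substitutes for the groups. Nor is it shown that most of the surplus had baseline data. If the T1 total of 32 is right, only 2 beyond the planned 30 did.

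The Control Intervention section says "half will receive only the control intervention" in the sentence that also gives a 2:1 ratio. That inconsistency is a separate matter, and nothing here relies on it.

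**Conclusion.** The point holds as a small loss of efficiency. The cap on controls has no stated purpose and, with the consents actually obtained, leaves about two patients randomised to control out of the comparison unless they replace a withdrawal. Following them would reduce the between-arm standard error by about 6% if all 36 consents count, by about 2% if only the 32 in the T1 total row do, and not at all with 30 consents. These figures assume equal SD in the arms, an exact 2:1 split and 20 filled group places; the percentage changes do not depend on the SD itself. The cap itself introduces no bias. Who is analysed after withdrawal and replacement is a different question and is not judged here.

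**What to change.** In the Allocation section, delete the selection of 5 per diagnosis and the substitute list for the control arm. State instead that every patient randomised to control is followed to T2 and analysed as a control. The substitute arrangement for the workshop groups can stay as it is. State also that experimental-arm substitutes are not moved into control after allocation.

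The ratio will then differ slightly by diagnosis (about 10 : 6.3 and 10 : 5.7 on the Table 1 consents), so the combined effect should be estimated within diagnosis and then pooled, not from the crude 20 v 12 means.

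The cost is revised wording plus T2 questionnaires and CA$20 payments for a few people who have already consented. Table 1 already reports T2 counts, so the change may mainly serve the definitive trial.

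An optional alternative for that trial is one random draw per diagnosis once baseline is complete, with everyone not drawn for the group becoming a control. On these counts it would give up to 16 controls (9 psychotic, 7 anxiety or mood) and an SE up to 13% smaller. It gives up the 2:1 ratio and the group substitutes, so a group that loses a member would run below 10. That is a trade-off for the investigators to weigh, not a correction.

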#### Principal Research Questions

The principal research questions are whether our novel PSWs-facilitated online intervention will have an impact in terms of (Q1) clinical recovery potential and (Q2) personal-civic recovery potential. We also question (Q3) how these potentials can be impacted by the COVID-19 pandemic and (Q4) how the lived experience of people in recovery can be mobilized to cope with the situation. Finally, we also explore (Q5) how sex and gender considerations can be taken into account for the pairing of PSWs with service users beyond considerations based solely on psychiatric diagnoses or specific MHPIs [35]. We aim to collect data for a future randomized controlled trial (RCT) [36] by clarifying a certain number of remaining uncertainties and by detecting an effect that would be specifically attributable to transitional peer support as facilitated by trained PSWs. We will thus consider scientific reasons, processes, resources, and management in preparation for a more definitive trial. Indicators of feasibility will include recruitment rates practices, participants and facilitators, as well as feasibility and retention rates in the study protocol [37].

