#### Recruitment

As of February 2020, 2136 IUSMM patients have been enrolled in the Signature Bank since the year 2012, including 822 individuals with psychotic disorders, and 853 with anxiety and/or mood disorders. The study was approved by the local ethics committee in accordance with the Declaration of Helsinki, and the Signature Bank’s management framework provides further details on recruitment and consent forms. Between August 26, 2019, and February 26, 2020 (6 months), a preliminary validation study [100] allowed us to recruit 93 of the Signature Bank participants diagnosed with either psychotic disorders, or with anxiety and mood disorders. In total, 36 were female (39%) and 57 were male (61%). They further completed the Recovery Assessment Scale and Citizenship Measure, both of which a 5-point Likert scale was used to rate items. For the former, the mean was 3.77 (out of 5; SD 0.78). For the latter, the mean was 3.91 (out of 5; SD 0.63). The type of participants we need can thus easily complete our questionnaires in parallel to those of the Signature Bank. A research assistant with lived experience of an MHPI will contact by phone all the above-mentioned 93 Signature Bank participants who have already been in touch for the previous validation study and who have already accepted to be contacted again by our team for such purposes. If needed, other Signature Bank participants who meet the inclusion criteria will also be contacted until 30 Information and Consent forms are returned. The Information and Consent form will be sent by email to those who provide an email address. They will be offered CA$20 as compensation indemnity for the baseline and follow-up completions of the Recovery Assessment Scale, the Citizenship Measure, and the Bem Sex Role Inventory (see the *Sex and Gender* section).

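### Replacing patients who withdraw after randomisation, and analysing only T1-plus-follow-up completers, lets the analysed set drift from the randomised set and overstates retention whenever a replaced patient leaves the denominator

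*Protocol article*

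**What the plan says.** The Allocation section of the protocol article places randomisation at consent: "Upon reception of the signed Information and Consent forms by email, consecutive referrals will be randomly allocated by computer algorithm". The arms are to hold 20 and 10 patients. A second draw follows within each arm: "Among those allocated to the experimental groups, 10 patients with psychotic disorders will be randomly selected to be part of the transitional support group", with 10 patients with anxiety or mood disorders chosen likewise. For controls, "It will be the same for the control group; 5 patients with psychotic disorders will be randomly selected", plus 5 with anxiety or mood disorders.

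Of the remainder, the section says that "those who have not been selected will be placed on a substitute list in the event of withdrawal of a selected patient". The withdrawn patient's place goes to a randomly drawn substitute from the matching list. No cut-off date or workshop number limits this.

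The Quantitative Analyzes section defines the analysed set: "All participants with data at baseline (T1) and follow-up will be included in the analyses". The article does not say that patients are analysed as randomised, or how a replaced patient is counted.

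The Principal Research Questions section lists among the feasibility indicators "feasibility and retention rates in the study protocol", in preparation for a larger randomised trial.

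**The concern.** A substitute may be drawn at random, but the withdrawal that opens the place is not random. It happens after allocation, in a trial where patients know whether they attend workshops, so the reasons for leaving can differ between arms. Replacing such a patient puts someone still willing to take part in the place of someone who was not, and the completers-only rule then removes whoever else was lost. The Discussion says that differences between the groups will in principle be attributable to the intervention, and the Abstract promises reliable evidence on effectiveness. Both statements need the groups to remain as randomised.

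In the experimental arm there is a further difficulty. The intervention is a fixed series of 10 weekly workshops, each opening on the written account of the last. With no time limit on substitution, a late substitute would receive only part of it.

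Retention is itself an output of this study. If a replaced patient drops out of the denominator, the rate handed to the planners of the larger trial is too high.

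**Working it through.** **Inputs (Results, Table 1).** Signed consent forms: 36 (17 anxiety/mood, 19 psychotic). T1 completers: 32 in the total row, but 16 + 19 = 35 from the subgroup rows. T2 completers: 10/10 psychotic experimental, 7/10 anxiety/mood experimental, 7/10 control. Numbers randomised, withdrawn and replaced: not reported.

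**Step 1: reproduce the article's figure.** Completers 10 + 7 + 7 = 24; places 10 + 10 + 10 = 30; 24/30 = 80.0%, as printed (exact 95% CI 61% to 92%).

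**Step 2: how many replacements were possible.** 36 − 30 = 6. By diagnosis, with 15 places each, that is 17 − 15 = 2 anxiety/mood and 19 − 15 = 4 psychotic. Using all six also requires each to be in the arm where a place fell vacant.

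**Step 3: retention by number replaced.** Suppose Table 1's 30 are the patients holding places at the end, and k others held a place, withdrew and were replaced. Then 30 + k patients were offered a place, and retention = 24/(30 + k):

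- k = 0: 24/30 = 80.0%
- k = 1: 24/31 = 77.4%
- k = 2: 24/32 = 75.0%
- k = 3: 24/33 = 72.7%
- k = 4: 24/34 = 70.6%
- k = 5: 24/35 = 68.6%
- k = 6: 24/36 = 66.7% (exact 95% CI 49% to 81%)

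The possible overstatement therefore runs from 0 to 80.0 − 66.7 = 13.3 percentage points. If only T1 completers could take a place, the floor is 24/32 = 75.0% using the total row, or 24/35 = 68.6% using the subgroup rows.

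**Step 4: completion by arm.** Experimental (10 + 7)/20 = 85%; control 7/10 = 70%.

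**Step 5: diagnosis mix among completers.** By design both arms are half psychotic. Among experimental completers the share is 10/17 = 58.8%. Table 1 does not split the control completers. With 5 + 5 controls and three missing, psychotic completers number between 2 and 5, so the share lies between 2/7 = 28.6% and 5/7 = 71.4%. The gap, experimental minus control, runs from 58.8 − 71.4 = −12.6 to 58.8 − 28.6 = about +30 points.

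**Step 6: what that could do to the pooled comparison.** Assume that mean change differs by 0.5 SD between diagnoses; the article gives no such figure. The mix alone then shifts the arm difference by between −0.126 × 0.5 = −0.06 SD and +0.302 × 0.5 = +0.15 SD. For scale, the standard error of an arm difference with 17 and 7 completers is √(1/17 + 1/7) = 0.45 SD, so the worst case is about a third of one standard error.

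The bias from arm-related replacement cannot be calculated, because neither the number of replacements nor the reasons for leaving are given.

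**The case against.** The strongest reply is that the article does not report that anyone was replaced. Table 1 labels 24/30 as T2 questionnaire completion rather than retention and prints the 36 consents beside it, and the article commits to CONSORT reporting. Replacements could also all have come before the first workshop, since Table 2 puts T1 in August 2020 and the groups in September to October. This stands as far as it goes: overstatement follows from the rule but is not shown to have happened. It does not rescue the rule, which sets no time limit and acts after allocation either way.

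Four stronger readings are tempting, and the document does not support them.

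- A reader might infer that true retention is 66.7%. Substitutes who were never called up are not dropouts, so 24/36 is only the floor.
- A reader might infer that stopping "until 30 Information and Consent forms are returned" leaves no substitutes. In the Recruitment section that limit attaches most naturally to the extra Signature Bank patients contacted if needed, after all 93 earlier participants have been phoned; 36 forms did come back.
- A reader might infer that allocation would seldom yield the 10/10/5/5 quotas. That presumes allocation blind to diagnosis, whereas the Allocation section says its blocks are meant to balance the strata. It does not define the strata, but diagnosis is the only grouping it uses.
- A reader might infer that the second draw itself biases the comparison. Random non-selection within an arm before treatment shrinks the set without biasing it.

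It is also fair to say that the diagnosis-mix effect is small against sampling error, and that it cannot arise in the separate within-diagnosis comparisons that the article also plans.

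**Conclusion.** The concern holds in a conditional form. The text itself establishes allocation at consent, replacement of withdrawals without a time limit, and analysis of T1-plus-follow-up completers only. Together these let the analysed set differ from the randomised set for reasons that can depend on arm. Retention is overstated whenever a withdrawn patient is replaced and left out of the denominator. On Table 1 the supportable range is 66.7% to 80.0%, and its position within that range depends on an unreported count of between 0 and 6 replacements. The lower end assumes that all six spare patients were used as replacements.

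Completion of 85% against 70% leaves the pooled completer comparison open to imbalance by diagnosis, worth −0.06 to +0.15 SD under the assumed 0.5 SD difference. That is a secondary matter. The replacement rule and the way retention is counted are what need correcting.

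**What to change.** For this study, where recruitment is over and only analysis and reporting can change:

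- State how many patients were randomised, withdrew and were replaced, by arm and diagnosis, and when each replacement occurred.
- Treat every replaced patient as a withdrawal. Report retention over all randomised patients who were offered a place, counting those replaced as lost.
- Analyse all randomised patients with available data in their allocated arm, with diagnosis in the model for the pooled comparison.
- Reconcile the T1 rows of Table 1 (32 against 16 + 19 = 35), since the retention floor depends on them.

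For the allocation text, and for the larger trial that will inherit it: allow substitution only before randomisation, and state explicitly that randomisation is 2:1 within diagnosis, so that the second selection becomes unnecessary.

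The cost is rewording of the Allocation and Quantitative Analyzes sections and a fuller participant-flow report. The downsides are that the retention figure may look less favourable and that, without replacement, a peer group may run with fewer than 10 members.
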